#### **8.3.3.3. Other Measurements of Interest**

No other measurements of interest are planned.

#### **8.3.4. Interim Analysis**

An interim analysis is not planned.

### **8.3.5. Key Elements of Analysis Plan**

The Analysis Plan will consist of summary and graphical displays. Individual patient listings will also be included. Full details will be described in a “Reporting and Analysis Plan” that is authored in accordance with SOP\_54838 v4 Development, Review and Approval of Reporting and Analysis Plan.s

#### **8.3.5.1. Quality of life analysis**

Quality of life data will be presented as number and percentage of subject in each answer category for a particular question, as well as overall score. Data will be presented for each visit (Baseline, end of 4-week treatment period).

#### **8.3.5.2. Safety Analyses**

All subjects who received at least one dose of study medication will be assessed for clinical safety and tolerability.

Clinical interpretation will be based upon review of displays of adverse events, laboratory values (hematology, chemistry, urinalysis), vital signs, 12-lead ECG, pulse oximetry, NT-ProBNP, physical examination, infusion site assessment, and pregnancy tests. Principal considerations in this evaluation of adverse events will be investigator-reported relationship of either adverse events or laboratory abnormalities to study medication. For each laboratory test, the number and percentage of subjects with values above the reference range will be displayed for each treatment group and overall. Appropriate monitoring of safety data will be conducted throughout the conduct of the study.

No formal statistical hypothesis testing is planned for safety parameters. All data will be presented descriptively or graphically.

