### **5.3. Blinding**

This will be a single-arm, open-label study and there will be no blinding.

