**Table 1      Time and Events Table (Continued)**

1. Follow-up visit should occur one week after Week 4 visit (Visit 3) for those subjects who are not participating in the extension phase of the study. For those continuing the treatment in the extension, follow up visit will occur at the end of extension study.
2. The first extension telephone call will be scheduled 3 months after baseline. Subsequent telephone calls will be scheduled every 6 months thereafter until the new FLOLAN diluent formulation is commercially available.
3. The first extension clinic visit will be scheduled 6 months after baseline. Subsequent clinic visits will be scheduled every 6 months thereafter until the new FLOLAN diluent formulation is commercially available.
4. Run-in period will start on the day of screening or up to 2 weeks after screening.
5. Subjects will remain in the clinic for a minimum of 6 hours (Day1) post dose or in the hospital for 24 to 48 hours (Days 1 to 2) post dose and then will be discharged from Baseline (Visit 2) per local guidelines and at the discretion of the investigator.
6. Hemodynamic parameters will only be collected at baseline (immediately prior to the switch) and at a single point between 1 to 2 hours after the switch in a subset of subjects where RHC is performed per local practice and per investigator. (see Section 6.1).
7. These safety assessments will be repeated just prior to discharge.
8. Clinical laboratory tests (clinical chemistry, haematology and urinalysis) may be repeated if there were results that were out of reference range from the previous visit or may be performed at the investigator's discretion.

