### 6.3.4. Clinical Laboratory Tests

The following tests are required at each clinic visit (including early withdrawal, an unscheduled visit and follow-up [if applicable]).

- **Chemistry:** serum alanine aminotransferase (ALT/SGPT), aspartate aminotransferase (AST/SGOT), alkaline phosphatase, gamma glutamyl transferase (GGT), lactate dehydrogenase (LDH), creatine phosphokinase (CPK), total bilirubin, creatinine, sodium, magnesium, potassium, chloride, bicarbonate (CO2), phosphorus-inorganic, calcium, blood urea nitrogen (BUN), uric acid, glucose, total protein, and albumin, thyroid function test (T3, T4 and TSH)
- **Haematology:** haemoglobin, hematocrit, red cell count, red cell indices (mean corpuscular volume [MCV], mean corpuscular haemoglobin [MCH], and mean corpuscular haemoglobin concentration [MCHC]), white blood cell count (total and differential), reticulocyte count, and platelet count.
- Dipstick urinalysis (to measure blood, glucose and protein).
- **Pregnancy:** Urine pregnancy test will be collected at screening, baseline, Week 4 or early withdrawal, and follow-up.

Blood samples for NT-Pro BNP concentration will only be collected at baseline, and at Week 4 or at early withdrawal (if applicable).

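### The only reference-range count stated for laboratory tests covers high values, so low haemoglobin, platelet, white-cell, electrolyte or albumin results do not enter it

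*Protocol*

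**What the plan says.** Section 8.3.5.2 of the protocol fixes the laboratory abnormality summary: "the number and percentage of subjects with values above the reference range will be displayed for each treatment group and overall". The sentence applies to each laboratory test without exception. The same section bases the safety interpretation more broadly on displays, with no direction stated: "Clinical interpretation will be based upon review of displays of adverse events, laboratory values (hematology, chemistry, urinalysis), vital signs".

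Section 6.3.4 lists what is measured. Haematology includes "haemoglobin, hematocrit, red cell count, red cell indices" and "white blood cell count (total and differential), reticulocyte count, and platelet count". Chemistry includes "creatinine, sodium, magnesium, potassium, chloride", as well as calcium, bicarbonate, glucose, total protein and albumin. A urine dipstick and a urine pregnancy test are listed too.

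Footnote 8 to the Time and Events Table (Table 1) uses two-directional language for repeat testing: clinical laboratory tests "may be repeated if there were results that were out of reference range from the previous visit".

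On the number of arms, Section 5.3 states: "This will be a single-arm, open-label study and there will be no blinding".

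**The concern.** A count of subjects outside the reference range is the summary a reader turns to first when asking whether laboratory results changed after a switch of formulation. If it counts one direction only, it suits tests where harm shows as a rise, such as liver enzymes. It does not suit tests where a fall is the safety signal. For haemoglobin, platelets, white cells and several electrolytes the low side matters at least as much as the high side. The protocol itself describes inhibition of platelet aggregation as a main action of epoprostenol, so a platelet summary that covers only high counts is an odd choice.

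Safety and tolerability is a secondary objective, and laboratory tests are named among the secondary measurements in Section 8.3.3.2. What is at stake is the completeness of that table. The validity of the study is not in question.

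**Working it through.** The protocol states no figure on this point, so there is nothing to recompute. The check is a comparison of sections.

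1. **Direction and scope of the count.** Section 8.3.5.2 reads "For each laboratory test, the number and percentage of subjects with values above the reference range". The direction is upward and the scope is every test. The sentence does not contain the word *only*. The conclusion therefore depends on whether another range-based count is stated elsewhere.

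2. **Search for a second count.** Section 8.3.3.2 lists laboratory tests as a measurement and allows presentation in total or by visit, but names no abnormality category. Section 8.3.5 promises summary and graphical displays and patient listings, with details in a Reporting and Analysis Plan. Section 8.3.5.4 does not cover laboratory tests. No section plans a count of subjects below, or more generally outside, the range. The high-side count is the only one stated.

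3. **Fit to the panel.** The protocol gives no reference ranges. I assume, as is usual, that haemoglobin, white cells, platelets, sodium, potassium, calcium, magnesium and albumin are reported against both a lower and an upper limit. For each of these, a subject below the lower limit satisfies the stated condition in no case and so is not counted.

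4. **Comparison with the rest of the protocol.** Footnote 8 of Table 1 treats a result out of range in either direction as a reason to repeat the test. Section 6.3.7 covers any abnormal result that the investigator considers clinically significant. Only the analysis sentence points one way. A low result can therefore prompt a repeat test without entering the abnormality count.

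5. **Grouping.** With a single arm (Section 5.3), a column for the one treatment group and a column for all subjects contain the same subjects. The phrase changes no number, but it does not describe this study.

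6. **Scale.** Section 4.1 plans about 20 subjects, with at least 15 completing. One subject is 1/20 = 5% of those enrolled, or 1/15 = 6.7% of the minimum number of completers. Each subject with a low value who goes uncounted is thus a visible share of the sample. How many there would be cannot be inferred from the document.

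**The case against.** The strongest reply is that low values still have several routes into the report. Section 8.3.5.2 provides displays of laboratory values without a direction. Section 8.3.5 provides listings, which for about 20 subjects can be read in full. Section 6.3.7 requires clinically significant abnormal results, in either direction, to be recorded as adverse events. This stands, and it rules out a stronger reading that a reader might infer, namely that the safety evaluation cannot see low values at all. It does not remove the point. Listings are not summaries, and means can hide a few low individuals. Adverse-event capture depends on judgement and leaves out findings associated with the underlying disease unless they are more severe than expected.

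A reader might also infer that the table would report no subjects with low values. It would not: it would show the high values and be silent on the low ones.

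A third tempting inference is that the plan cannot separate results before the switch from those after it. Section 8.3.3.2 already allows by-visit presentation, although it offers this as an alternative to a total over the whole treatment period. Naming the visits in the corrected sentence settles that choice; the existing text is not an error on this count.

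Finally, it can be said that details belong in the Reporting and Analysis Plan, which is not at hand. That holds for shift tables and table layout, whose absence is no fault of the protocol. It does not hold for the direction of the count, which the protocol fixes itself. An analysis plan that follows it inherits the gap, and one that departs from it contradicts the protocol.

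**Conclusion.** The point holds in a limited form. The one reference-range summary that the protocol specifies counts high values and omits low values for tests with a two-sided range, and it is out of step with the two-directional wording of footnote 8. The effect is an incomplete safety table in a descriptive study; low values remain available through other displays, listings and adverse-event reports. No numerical size can be attached, because the protocol gives no expected frequency of low results. The mention of treatment groups is a wording slip that alters no result and adds no weight.

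The conclusion rests on two assumptions: that the listed tests carry a lower reference limit in the laboratories used, and that the sentence in Section 8.3.5.2 is meant to be followed as written. It is a clear correction worth making, and a cheap one.

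**What to change.** Rewrite the sentence in Section 8.3.5.2 to this effect: *for every test with a numeric reference range, show how many subjects (and what percentage) fall below the range and how many fall above it, separately, at screening, baseline and Week 4 or early withdrawal.* Delete the phrase about treatment groups and overall.

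Restricting the rule to numeric ranges keeps out the dipstick and the urine pregnancy test, for which a below-range category has no meaning. A follow-up column is best left to the Reporting and Analysis Plan. Under footnotes 1 and 8 of Table 1, follow-up laboratory tests are optional, and the visit falls one week after Week 4 for some subjects and at the end of the extension for others. Percentages there would come from a selected group at mixed times. A shift table from baseline can be decided in the same plan.

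The cost is one amended sentence and a slightly larger standard table. The tests are already scheduled at the visits named, so no new data are needed.

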### Secondary

Safety and tolerability will be assessed based on a review of the following parameters:

- Adverse events
- Serious Adverse Events
- Vital signs: systolic and diastolic blood pressure, heart rate
- Clinical laboratory tests (clinical chemistry, hematology, and urinalysis)
- Infusion site reactions including erythema, excoriation, induration, skin necrosis or signs of local sepsis

Efficacy will be assessed based on a review of the following parameters:

- Six minute walk distance test (6MWD) after 4-weeks of treatment
- Breathlessness after 6MWD – Borg Dyspnoea Index (BDI)
- World Health Organization [WHO] functional class at baseline and after 4-weeks of treatment

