## 4.2. Inclusion Criteria

Specific information regarding warnings, precautions, contraindications, adverse events, and other pertinent information on the GSK investigational product or other study treatment that may impact subject eligibility is provided in the product label.

Deviations from inclusion criteria are not allowed because they can potentially jeopardize the scientific integrity of the study, regulatory acceptability or subject safety. Therefore, adherence to the criteria as specified in the protocol is essential.

Subjects eligible for enrolment in the study must meet all of the following criteria:

1. Adult male or female at least 18 to 75 years at the time of screening.
2. Subjects must have been on FLOLAN therapy for pulmonary arterial hypertension (PAH) as approved in the product label.
3. Subjects must be on stable doses of their existing FLOLAN treatment for a minimum of 3 months prior to screening;
4. Subjects must be on stable doses of any current PAH treatments other than FLOLAN in the last 30 days;
5. Subjects must walk a distance of at least 150 meters during six-minute walk distance test (6MWD). This test must be completed during the Screening Visit;
6. A female subject is eligible to participate if she is of:
  - Child-bearing potential must have a negative urine pregnancy at screening and baseline and agrees to use one of the contraception methods listed in Section 6.3.5 for an appropriate period of time (as determined by the product label or investigator) prior to the start of dosing to sufficiently minimize the risk of pregnancy at that point. Female subjects must agree to use contraception until the end of follow-up visit.
  - Non-childbearing potential defined as pre-menopausal females with a documented tubal ligation or hysterectomy; or postmenopausal defined as 12 months of spontaneous amenorrhea [in questionable cases a blood sample with simultaneous follicle stimulating hormone (FSH) > 40 MIU/ml and estradiol < 40 pg/ml (<147 pmol/L) is confirmatory].
7. Subjects must be competent to understand the information given in the Institutional Review Board (IRB) or Independent Ethics Committee (IEC) approved informed consent form and must sign the form prior to the initiation of any study procedures.

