### **5.2. Treatment Assignment**

All Subjects will be receiving the new thermo stable formulation of FLOLAN during the treatment phase.

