#### **8.3.3.2. Secondary Measurements of Interest**

The secondary measurements of interest are the following:

- Hemodynamic parameters (Mean Pulmonary artery blood pressure in mmHg [mPAP], Right Vascular resistance [PVR], Cardiac Index [CI], Right Atrial Pressure [RAP].
- Six minute walking distance (6MWD)
- Breathlessness after 6MWD – Borg Dyspnoea index
- Who functional class
- Adverse events and Serious adverse events
- Vital signs: systolic and diastolic blood pressure, heart rate
- Clinical laboratory tests (clinical chemistry, hematology, and Urinalysis)
- 12-lead ECG
- Oxygen saturation
- Infusion site reactions including erythema, excoriation, induration, skin necrosis, or signs of local sepsis
- Urine pregnancy test

All data will be presented in total for the whole treatment period or by visit, where available.

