#### **8.3.5.4. Other Analyses**

All other data (demography, medical history, disease history, therapy history, concomitant medications, exposure, compliance to study drug, infusion site assessment) will be summarized descriptively, and by visit, where available.

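### The laboratory display fixed in section 8.3.5.2 is split by treatment group in a single-arm switch study and does not separate abnormalities present before the switch from those that arise after it

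*Protocol*

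**What the plan says.** Protocol section 8.3.5.2 (Safety Analyses) names one summary for laboratory data: "the number and percentage of subjects with values above the reference range will be displayed for each treatment group and overall". Section 5.3 says "This will be a single-arm, open-label study and there will be no blinding", and section 5.2 says "All Subjects will be receiving the new thermo stable formulation of FLOLAN during the treatment phase".

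Section 8.3.3.2 lists laboratory tests and infusion site reactions among the secondary measurements and adds: "All data will be presented in total for the whole treatment period or by visit, where available". Section 8.3.5.4 covers a list of other data that ends with "infusion site assessment) will be summarized descriptively, and by visit, where available". The Protocol Summary gives the infusion-site endpoint as "Infusion site reactions including erythema, excoriation, induration, skin necrosis or signs of local sepsis".

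In Table 1, laboratory tests and infusion-site assessment are both marked at Screening, Baseline (Visit 2) and Week 4. For the infusion site, vital signs and adverse events at Visit 2, a footnote adds: "These safety assessments will be repeated just prior to discharge". Section 8.3.5.3 provides for change from screening or baseline, but under efficacy only. Section 3.2 gives the comparison of baseline with after treatment as the reason for enrolling stable subjects.

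**The concern.** The laboratory sentence reads as if written for a trial with parallel arms, where the other arm shows how many abnormalities to expect anyway. Here the only reference is the subject's own status on the old formulation. That status is recorded, but the stated rule does not use it: a subject above range at Baseline and unchanged at Week 4 is counted in the same way as one who moved above range after the switch.

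Pre-existing findings are plausible in this population. Section 4.2 requires that "Subjects must be on stable doses of their existing FLOLAN treatment for a minimum of 3 months prior to screening", and a 4-week run-in on the old formulation follows. Safety and tolerability of the new formulation is the first secondary objective. In about 20 subjects, a reader will want to know whether one, two or three people changed after the switch, and the stated count does not say.

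**Working it through.** The plan states no figure on this point: there is no test, power or margin, and the sample size was set by feasibility. The check is therefore of the wording first, and then of what the counts can and cannot show.

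**Wording against design.** With one arm (5.2, 5.3), the number for the single treatment group equals the overall number, so the two columns are identical. Section 3.1 does define regimen A (run-in, old diluent) and regimen B (treatment, new diluent). If *group* was meant as regimen, 8.3.5.2 does not say so, and two regimen columns would still be separate counts with no link within subject.

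**Whole-period total.** Inputs: n = 15 completers or 20 enrolled (section 4.1). The share p0 of subjects with a given abnormality before the switch is not in the document and is assumed to lie between 5% and 40%. Suppose every such abnormality persists and the switch causes none.

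- Expected count after the switch = n × p0.
- Chance that at least one subject is counted = 1 − (1 − p0)^n.

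| p0 | Expected, n = 15 | Chance of at least one, n = 15 | Expected, n = 20 |
|---|---|---|---|
| 5% | 0.75 | 54% | 1 |
| 10% | 1.5 | 79% | 2 |
| 20% | 3.0 | 96.5% | 4 |
| 30% | 4.5 | 99.5% | 6 |
| 40% | 6.0 | over 99.9% | 8 |

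A total for the treatment period, shown without the pre-switch count, can therefore consist entirely of carried-over abnormalities.

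**By-visit counts.** These do show the Baseline count beside Week 4. Let b be the number abnormal at Baseline and w the number at Week 4, among n subjects with both values. The number newly abnormal then lies between max(0, w − b) and min(w, n − b), out of n − b subjects who were normal at Baseline. With n = 15 and assumed b and w (exact Clopper-Pearson 95% intervals):

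| b | w | Fewest newly abnormal | Most newly abnormal |
|---|---|---|---|
| 3 | 3 | 0/12 (0 to 26.5%) | 3/12 = 25% (5.5 to 57.2%) |
| 4 | 5 | 1/11 (0.2 to 41.3%) | 5/11 (16.7 to 76.6%) |
| 6 | 6 | 0/9 (0 to 33.6%) | 6/9 (29.9 to 92.5%) |

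In the first row, the same two counts fit three subjects who were abnormal throughout. They also fit three who resolved and three others who became abnormal. A within-subject cross-tabulation shows which of these happened.

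**Infusion site.** Table 1 places one inspection at Visit 2 and repeats it before discharge, after the switch. A table by visit alone puts an old-formulation and a new-formulation record under the same visit.

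**The case against.** The strongest reply is that shift tables and rules for treatment-emergent findings commonly belong in an analysis plan. Section 8.3.5 defers full details to a Reporting and Analysis Plan, which is not shown. Section 8.3.5.2 names one display without saying it is the only one, and section 8.3.3 plans no formal comparisons. On this view only a slip of wording remains. Part of this stands: the absence of shift tables from the protocol would not by itself be a finding. But the protocol did not leave the laboratory display open. It specified one that does not fit the design, and a plan written faithfully to it would inherit the problem.

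A reader might also infer that abnormalities present on the old formulation will be reported as findings on the new one. The documents do not support that:

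- by-visit displays would include Screening and Baseline;
- individual listings are planned (8.3.5), and about 20 subjects can be followed one by one;
- adverse events are collected only from the start of study treatment (6.3.9);
- the rule for recording abnormal results as adverse events refers to worsening from baseline (6.3.7);
- 8.3.5.2 makes the investigator's view of the relationship to study medication a principal consideration.

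These safeguards stand and limit the harm. They do not repair the summary itself, because listings support case review but give no count of new onset.

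A reader might further infer that infusion-site data share the treatment-group error. They do not: that wording applies to laboratory tests only, and infusion-site assessment is summarised by visit. Nor would it help to add up chance abnormalities over the whole laboratory panel. The stated display is per test, and chance results in healthy people say nothing about abnormalities that persist.

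**Conclusion.** The point holds in a limited form. The laboratory display in 8.3.5.2 conflicts with the single-arm design and makes no use of the pre-switch values that the protocol collects. Neither by-visit counts nor a whole-period total identifies new onset: in the assumed case of 3 of 15 at both visits, the answer lies anywhere from 0/12 to 3/12. No hypothesis test is affected, and the safeguards above make it unlikely that a serious individual case would be missed. What is lost is a usable summary for the first secondary objective.

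The numerical illustrations rest on assumed prevalences and counts, on 15 subjects with values at both visits and, for the carry-over table, on full persistence. The proposed comparison also assumes that the Visit 2 laboratory sample is taken before the switch, the order in which section 3.1 lists the two steps. The infusion-site point is secondary.

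**What to change.** In section 8.3.5.2, delete the split by treatment group and overall, and replace the sentence with wording such as: *For each laboratory test, status relative to the reference range at Week 4 and at the worst post-switch value will be cross-tabulated against the last pre-switch (Baseline) status. The number and percentage of subjects newly abnormal or worsened since Baseline will be displayed.*

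As a secondary change, label the two Visit 2 infusion-site inspections as pre-switch and post-switch, and state in 8.3.5.4 that new or worsened findings since the pre-switch inspection will be counted.

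The cost is a wording change and one standard shift-table program. Both sets of assessments are already in Table 1, so no new data are needed.
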